#### Criteria for discontinuing or modifying allocated interventions {11b}

Caregivers and adolescents may withdraw from the study and/or interventions at any time without any consequences. All data up to the point of withdrawal will be retained unless requested otherwise. If we determine that participants or their families have experienced significant harm (i.e. abuse, suicidality, intimate partner violence, or other potential psychological or physical injuries) as a result of participation in the study or interventions, we will cease activities until these issues can be addressed adequately.

#### Strategies to improve adherence to interventions {11c}

Caregivers in the intervention and control groups will receive a low-cost locally sourced smartphone for use during the trial. While smartphone access in Tanzania is currently at 38%, the telecommunications sector is experiencing rapid growth, and the government plans to increase smartphone-based internet access to 80% of the population by 2025 [46]. Following pragmatic trial principles [47], we therefore aimed for a sample that reflects smartphone access levels at the trial end date of 2025, rather than at the start date of 2023. Caregivers will be able to keep the phone after the end of the study.

ParentApp stores digital engagement data, which will be shared automatically when the device is connected to the internet and monitored during the trial. To collect this data, as well as participate in WhatsApp activities where relevant, caregivers will be provided with monthly data bundles for the duration of the study to enable app usage and data syncing, up to 1 GB total per month (around $0.70).

#### Relevant concomitant care permitted or prohibited during the trial {11d}

Participants are not restricted from receiving other care during the trial period.

#### Provisions for post-trial care {30}

The risk of participants experiencing any adverse events during this trial because of the interventions is very low. However, we will employ safeguarding procedures to mitigate risks of adverse effects. Where any participant discloses information which shows them or others to be at risk of significant harm, the research team will make direct referrals to relevant service providers. The referral process will be triggered through participant survey responses that indicate potential harmful experiences and/or support needs (e.g. violence, severe mental ill-health, neglect). Direct referrals to in-person social services will also be available through the implementing partner, should these be requested by participants. ParentApp includes national self-referral and emergency contacts which are affordable and remote-friendly, should families require further support during or after the trial. These resources were identified by the research and implementing teams following a thorough mapping of online and affordable support systems in Tanzania.

### Outcomes {12}

#### Adolescent and caregiver outcomes

Collection of data on adolescent and caregiver outcomes will take place at three time points: baseline, 1 month post-intervention (4 months post-baseline), and 12 months post-intervention (16 months post-baseline). Outcome measurements will be reported independently by caregivers and adolescents, unless specified otherwise. Standardised measurements and standard timeframe of events or practices over the “past 4 weeks” will be used to strengthen study validity and identify potential changes in behaviour due to the intervention. The outcomes will be informed by behaviour change theoretical components and the veracity of these will be assessed empirically. All measures are translated into Kiswahili and back translated to check accuracy. Some measures have adaptations made for comprehensibility and contextualisation, after feedback from their use in the pre-post pilot for this trial.

##### Primary outcomes

*Child maltreatment (physical and emotional abuse)* will be assessed using the relevant subscales of the Caregiver and Child Versions of the International Society for the Prevention of Child Abuse and Neglect Screening Tool for Trials (ICAST-Trial) [48]. *Sexual violence risk and victimisation* (adolescent report only) will combine measures of contact and non-contact sexual abuse, and exposure to high-risk situations for abuse, and be evaluated using a combination of items from different tools: the ICAST-Trial [48], measures used in the CDC Violence Against Children and Youth Surveys [49], and a locally derived risk scale developed in consultation with families and practitioners.

##### Secondary outcomes

*Poor parental supervision*, *inconsistent discipline*, *positive parenting* and *positive involved parenting* will be assessed using the relevant subscales from the Alabama Parenting Questionnaire [50].*Neglect* will be measured using an adapted version of the neglect subscale from the ICAST-Trial Caregiver and Child Versions [48].Measures of caregiver and adolescent *attitudes to physical punishment* using an item from the UNICEF Multiple Indicator Cluster Surveys (MICS) 5 Child Discipline module [51].*Family-level planning to reduce risks of sexual violence* victimisation will be assessed using an item developed in South Africa for a randomised trial of the in-person PLH Teens programme [20].*Intimate partner violence (IPV) experience, witnessing* (adolescent report only) and* perpetration* (caregiver report only) will be measured using items adapted from the WHO’s Violence Against Women Instrument (VAWI) used in the WHO Multi-Country Study on Domestic Violence [52], and items from the ICAST-Trial Child Version [48].*Gender equitable behaviours* (caregiver report only) will be measured using four items adapted from questionnaires used in previous violence prevention studies: Three items are adapted from a questionnaire that was developed by researchers at the London School of Hygiene and Tropical Medicine (LSHTM) and used in an RCT of a violence prevention intervention in Tanzania [53]. The fourth item is adapted from a questionnaire developed by researchers of an RCT of a gender-transformative violence prevention intervention in Rwanda [54].Caregiver and adolescent *attitudes towards gender roles and IPV* will be measured by self-report using items adapted from the ‘Attitudes towards gender roles’ section of the WHO Multi-Country Study on Domestic Violence [52].*Caregiver support for school* is measured through five items assessing parent involvement and support of education [55].*P**arent communication* is measured using items adapted from the Parent–Child Communication Scale used in the Fast Track Intervention Study [56].*Economic hardship* is measured using items on monthly shortfalls of basic necessities, such as clothes, soap, and school equipment (reported independently by both caregivers and adolescents).*Financial self-effi*cacy and *family financial management* are measured using items on borrowing (from loan sharks and others), saving and budgeting.*Parenting stress* (caregiver report only) will be assessed using the Parental Stress Scale [57].Caregiver and adolescent *mental health distress* will be evaluated using the Patient Health Questionnaire 4 (PHQ-4), a brief four-item screening for symptoms of anxiety and depression [58].*Social support* for caregivers (reported by caregivers) and adolescents (reported by adolescents) will be measured using the Medical Outcomes Study Social Support Survey [59].*Sexual risk behaviour* (adolescent report only) measures are adapted from the CDC Violence Against Children and Youth Surveys (VACS) and the South African Demographic and Health Survey [60]. One item on age-disparate sex was included.Components will be interrogated in alignment with theoretical models of behaviour change.

##### Other pre-specified and exploratory outcomes

*Use of internet and exposure to online violence risk* will be evaluated using items adapted from the Global Partnership to End Violence Against Children’s Disrupting Harm project [61]. *Digital literacy*, measured by questions developed by the research team, will assess technical, social, critical, and creative digital skills. *Adolescent externalising and internalising behaviour* are measured using the Child and Adolescent Behaviour Inventory (CABI) [62] and reported by caregivers only. *Substance use* is reported by caregivers and adolescents using items adapted from the WHO Alcohol Use Disorders Identification Test [53] and the WHO Global School-based Health Survey [54].

The concept of *engaged responsive parenting* will be used as a uniting concept covering the cross-cultural indicators of playful learning [63], characteristics of learning through play [64, 65], and positive parenting. Engaged responsive parenting will be measured by combining items from the APQ positive parenting and involvement subscales, the parent–child communication scale (caregiver only) and parent support for school. Caregiver’s engagement with playful activities in the app (e.g. number of playful activities completed) will be measured through app engagement data.

#### Socio-demographic measures

Socio-demographic variables measured at baseline include age, gender, assessment of disability (also assessed at 1 month follow-up), assessment of basic literacy, household structure, adolescent’s relationship to the caregiver, household employment, school enrolment, relationship status and orphanhood. Demographic factors to be measured include general questions as well as items from the Multiple Indicator Cluster Surveys (MICS) [51]. We will assess access to social protection (e.g. government cash transfers) to explore whether combined social protection and parenting support is associated with improved parent and child outcomes.

#### Cost-effectiveness outcomes

Cost-effectiveness outcomes will include facilitator and participant app engagement, measuring time spent and data costs incurred, as well as delivery costs (e.g. provision of devices, facilitator training and support, app maintenance, programme onboarding) and intervention costs (e.g. WhatsApp group support). Cost data will be collected through weekly Open Data Kit (ODK)-based surveys with facilitators. Facilitators will record time and data usage of prescribed intervention efforts, as well as basic participant engagement statistics. A visual analogue scale from 0 to 100, administered at baseline and follow-up with caregivers and adolescents, will be used to approximate quality-adjusted-life-years (QALY) to support long-term cost-effectiveness measures. Modelling maltreatment outcomes over time and the associated QALYs linked to these will support long-term cost-effectiveness analyses. We will adopt a multi-outcome discounted cost-effective analysis methodology, in order to better understand the cost and savings of a single intervention (ParentApp) across multiple sectors and violence against children pathways [66, 67].

#### Implementation outcomes

Engagement data, such as the amount, frequency, and duration of usage, is collected automatically through the intervention and control apps and used to examine programme fidelity, exposure, and adherence. It includes measures of engagement with the app (e.g. number of times the app is opened, time spent on the app), engagement with the content and skills (e.g. number of modules completed, number of activities completed, positive behaviours logged), and other engagement measures (e.g. types of content accessed).

Implementation will further be assessed through implementer records of activities and weekly Open Data Kit survey with implementing partner facilitators. Facilitators will record basic participant engagement statistics, as well as brief notes on challenges and successes encountered in programme delivery. To assess the quality of support, a random sample of the live chat sessions in the moderated WhatsApp groups will be monitored. It will be explained to caregivers that the purpose of the monitoring is to assess facilitator skills and ensure that they are getting the best possible service.

#### Intervention acceptability, benefits, and challenges

To complement the quantitative analyses, we will conduct qualitative interviews with adolescents, caregivers, and programme staff. Interviews with caregivers and adolescents will explore participant satisfaction and engagement with ParentApp; participant perspectives on ParentApp’s acceptability and cultural relevance; experiences of delivery, and their perceived benefits and challenges of the programme. Interviews with programme staff will explore their experiences of supporting ParentApp users, benefits, and challenges of delivering the programme. Questions will address delivery contexts and implementation processes, barriers and facilitators experienced during implementation, and recommendations for future implementation. Where appropriate, focus groups will be conducted with staff.

#### Exploratory interviews with siblings

If additional funding is obtained, an additional exploratory set of interviews will take place. Between 1-month post-test and 12-month follow-up stages, adolescent siblings, or other adolescent co-residents in the household to the participating adolescents will be interviewed using the same questionnaire as the 1-month post-test. This would allow exploratory endline-only analysis to begin to understand whether a parenting intervention could have benefits for more than one young person in a household.

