### Eligibility criteria {10}

Three types of participants will be recruited for the trial—caregivers, adolescents, and implementing partner staff. Caregivers and adolescents will be recruited from eligible clusters, which include sub wards in the Mwanza region. Sub wards are defined as the lowest administrative structure at the community level in urban settings in Tanzania.

Inclusion criteria for participating caregivers within the selected clusters:Age 18 years or older,Primary caregiver currently caring for an adolescent between the ages of 10 and 17 years,Staying in the same household as the adolescent at least four nights a week in the past month,Basic literacy, which will be determined during screening using the following question: “How do you find reading?”. Participants who respond that they “can read with a little difficulty” or “can read easily” will be included whereas those who respond that they “can’t read at all” or “can read but with lots of difficulty” will be excluded.In agreement to participate in either the ParentApp (intervention) or WASH App (control) programme, andHas provided written and/or oral informed consent to participate in the full study.

Inclusion criteria for participating adolescents:Age 10–17 years,The dependent of a parent or caregiver who meets the above inclusion criteria and participates in the trial,Has provided written and/or oral assent to participate in the full study, andPrimary caregiver has provided written and/or oral consent for the adolescent to participate in the full study.

If there are multiple adolescents in the household, the caregiver is asked to select the adolescent whose ‘behaviour is giving them the most problems.’ Selection of the index teen is not based on gender and there are no efforts to balance the number of male and female adolescents in the trial.

Implementing partner staff will be eligible to participate in the study if they are:Aged 18 or older,Previous participants of the ParentApp facilitator training workshop, andAble to provide written and/or oral informed consent to participate in the study.

Any participant exhibiting severe mental health problems or acute mental disabilities that mean they are unable to give informed consent will be excluded from the study for ethical reasons.

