### Sample size {14}

The study will recruit approximately 2400 caregiver-adolescent dyads (i.e. 2400 caregivers and 2400 adolescents) to take part in the RCT; of these, between 40 and 60 caregivers and between 20 and 30 adolescents will also participate in an individual post-programme qualitative interview. The sample size was determined by power calculations from the pilot study, using multilevel Poisson regression.

modelling. These suggest that if the outcome scale generates a control group mean of 4 and an effect size of 0.95, and accounting for attrition in both the trial and the programme, to get 80% power a minimum of 80 clusters with 30 families in each cluster is required (i.e. 2400 caregiver-adolescent dyads). Semi-structured qualitative interviews will also be conducted with 10 staff responsible for programme delivery at each of the implementing organisations. Adolescent siblings or co-residents in the household in an estimated 50% of households will be assessed at endline only.

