## Assignment of interventions: blinding

### Who will be blinded {17a}

The implementing partner will notify the participating families of their allocation status after baseline data collection in their cluster is complete to assure that participants are blind to allocation during the baseline assessments. The allocation status of participating families in other clusters will be concealed from participants, thus reducing the potential for contamination. Based on prior trials of parenting programmes, we do not anticipate that blinding will be possible for research staff after baseline data collection as families usually mention their participation in the intervention or control programme. Similarly, of course, participants cannot be blind to their own treatment condition. However, the data analysts will be blinded from condition assignment during analysis.

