#### Quantitative data collection

##### Baseline and follow-up surveys

All outcomes of intervention effectiveness will be measured at baseline, 1-month post-intervention, and at 12-month follow-up. Interviews with adolescent siblings or co-resident adolescents will take place at endline only (between 1-month and 12-month follow-up) in households where there is more than one adolescent.

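### The exploratory sibling comparison draws its sample after allocation, in unblinded homes and with no sibling baseline, so participation that differs by arm could create or hide an effect

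*Protocol article*

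**What the plan says.** The section Exploratory interviews with siblings states that "adolescent siblings, or other adolescent co-residents in the household to the participating adolescents will be interviewed using the same questionnaire as the 1-month post-test". It places these interviews between the two follow-up surveys, calls the resulting analysis exploratory and endline-only, and opens with a condition: "If additional funding is obtained, an additional exploratory set of interviews will take place".

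Two other sections describe the same work without that condition. Sample size {14} says: "Adolescent siblings or co-residents in the household in an estimated 50% of households will be assessed at endline only". Baseline and follow-up surveys repeats the timing and limits the interviews to homes "in households where there is more than one adolescent".

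Implementation {16c} has each block of clusters randomised once its baseline data are in. Who will be blinded {17a} then says of the period that follows: "we do not anticipate that blinding will be possible for research staff after baseline data collection". The same section notes that participants cannot be blind to their own condition, and Procedure for unblinding {17b} confirms that neither group is blinded after baseline.

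Socio-demographic measures lists household structure among the variables collected at baseline.

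**The concern.** The caregiver-adolescent dyads are enrolled and assessed before their cluster is allocated, so knowledge of the arm cannot affect who is in the main comparison at entry. The siblings lack that protection. They are approached months later, by staff who probably know the arm and in families who certainly do. As written, the sample is whoever is a sibling or adolescent co-resident at the time of the visit.

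Arm-dependent selection can enter in three ways: adolescents may move in or out after allocation, someone may choose among several in the home, and the caregiver or adolescent may refuse. The siblings' own outcomes are not measured at baseline, so the analysis cannot condition on where they started.

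The sub-study asks whether benefit extends to other young people in the home. If participation depends on both arm and level of abuse, the comparison cannot separate such a benefit from selection.

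**Working it through.** **Planned scale.** Sample size {14} gives 80 clusters of 30 families: 80 × 30 = 2400 dyads. The article's 50% of households gives 0.5 × 2400 = 1200 households, which is 1200 / 2 = 600 per arm and 1200 / 80 = 15 per cluster. No sample size, power or target effect is stated for siblings, so there is no planned sibling figure to reproduce.

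**Order of events from the article.**

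1. Households enrol and the caregiver names the index adolescent (Eligibility criteria {10}).
2. Baseline data are collected for the block, including household structure.
3. The block is randomised (Implementation {16c}).
4. Families learn their arm, and staff are expected to learn it (Who will be blinded {17a}).
5. The 1-month survey takes place.
6. Siblings and co-residents are interviewed for the first and only time.
7. The 12-month survey takes place.

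Households are fixed at steps 1 and 2. The persons interviewed at step 6 are not, because no section requires residence at baseline or says whether all or only one is taken.

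**Size of possible bias (illustration).** The article gives no sibling uptake or outcome distribution, so every input here is assumed:

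- The overall sibling mean is 4, borrowed from the control mean in Sample size {14}.
- 30% of siblings are in a high-abuse group with mean 8. The other 70% then have mean (4 − 0.3 × 8) / 0.7 = 2.29.
- There is no true effect (ratio 1.00).
- Participation is 90% in both groups of the control arm and in the low group of the intervention arm. It is r in the high group of the intervention arm.

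Observed control mean = 4.00. Observed intervention mean = (0.3 × r × 8 + 0.7 × 0.90 × 2.29) / (0.3 × r + 0.7 × 0.90) = (2.4r + 1.44) / (0.3r + 0.63). Overall intervention uptake is the denominator, 0.3r + 0.63.

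| r | Overall uptake, intervention (control 90%) | Observed mean | Apparent ratio |
|---|---|---|---|
| 0.90 | 90.0% | 3.60 / 0.900 = 4.00 | 1.000 |
| 0.85 | 88.5% | 3.48 / 0.885 = 3.93 | 0.983 |
| 0.80 | 87.0% | 3.36 / 0.870 = 3.86 | 0.966 |
| 0.75 | 85.5% | 3.24 / 0.855 = 3.79 | 0.947 |
| 0.70 | 84.0% | 3.12 / 0.840 = 3.71 | 0.929 |
| 0.60 | 81.0% | 2.88 / 0.810 = 3.56 | 0.889 |

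If the shortfall falls in the control arm instead, the ratios invert, from 1 / 0.983 = 1.02 to 1 / 0.889 = 1.125, and could hide a true benefit. If the two groups have the same mean, or if participation falls equally in both, the ratio is 1.00 whatever the uptake.

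In the row for r = 0.75 the gap in overall uptake is only 90.0 − 85.5 = 4.5 points. Overall uptake by arm is therefore not enough on its own; the characteristics of those interviewed and not interviewed are needed too.

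**The case against.** The strongest reply is that the article already states the limits: the work is exploratory, endline-only and dependent on funding, and no hypothesis under Objectives {7} mentions siblings. That stands, and it is why the point is minor.

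Several stronger readings are tempting, but the article does not support them.

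- *Siblings become eligible only after allocation.* No section says so. Households and index adolescents are fixed beforehand, and many siblings will already live there. Bias can enter only through later moves, choice within the home, or refusal.
- *There is no selection rule.* There is one at household level: homes "in households where there is more than one adolescent". The plural wording can even be read as taking every sibling. Only the rule within the household is open, and an article may leave that to the full protocol.
- *Imbalance cannot be seen or adjusted.* That is true only of the siblings' own measures. Baseline data on the household, caregiver and index adolescent allow imbalance to be examined and partly corrected.
- *Co-residents breach the eligibility criteria.* The criterion "The dependent of a parent or caregiver who meets the above inclusion criteria and participates in the trial" governs adolescents in the dyads. The sibling study describes a different population, so a wider definition is a choice and not a contradiction.
- *The interviews disturb the 12-month primary outcome by triggering referrals.* Referral after a survey response applies in both arms, and nothing in the article indicates a differential effect.

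What survives is the timing, the lack of blinding and a sampling frame not anchored at baseline. These are choices the article itself states or leaves open, and the baseline data needed to improve on them are already being collected.

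**Conclusion.** The concern holds in limited form. The arm comparison of siblings and co-residents is open to identification and participation bias that the dyad comparison avoids at entry.

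The size of the bias cannot be known from the article. The range of 0.98 to 0.89 rests wholly on the assumed 30% high-abuse share, the means of 8 and 2.29, and 90% participation elsewhere; with non-participants like participants the bias is nil. A reader might set these ratios against the trial's planning effect of 0.95 and conclude that bias would swamp it. The article does not say on what scale 0.95 is expressed and sets no target effect for siblings, so that comparison is not warranted.

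Separately, the status of the interviews is inconsistent: one section makes them conditional on funding and two state them as planned. This is an editorial fault that needs correcting in any case.

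The primary and secondary conclusions of the trial are not affected.

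**What to change.** 1. Define eligible siblings from the household data collected before randomisation: adolescents aged 10–17, other than the index adolescent, who were co-resident at baseline.
2. State in advance whether all of them are interviewed or one per household chosen at random from that list.
3. Use the list as the denominator. Report uptake by arm, with baseline household and index-adolescent characteristics of those interviewed and not interviewed.
4. Adjust the sibling comparison for those baseline values, and say that the adjustment is partial because siblings have no baseline of their own.
5. Reconcile Sample size {14} and Baseline and follow-up surveys with the funding condition in Exploratory interviews with siblings.

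The cost is protocol wording plus a list drawn from data already held. Because those data predate allocation, the list can still be made after randomisation. There are two downsides. Adolescents who join the household later are left out. If the baseline household data lack ages, a short roster check is needed; done after allocation, it should ask about residence at baseline and would be somewhat weaker than a list made beforehand.
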